**Methods/Design:**

Twenty patients undergoing treatment with radiofrequency or microwave ablation for (recurrent) CRLM will be included in this prospective trial. During the first year of follow-up, patients will be scanned at the VU University Medical Center at 3-monthly intervals using a 4-phase liver CT, FDG PET-CT and FDG PET-MRI. Patients treated with chemotherapy <6 weeks prior to scanning or with a contra-indication for MRI will be excluded. MRI will be performed using both whole body imaging (mDixon) and dedicated liver sequences, including diffusion-weighted imaging, T1 in-phase and opposed-phase, T2 and dynamic contrast-enhanced imaging. The results of all modalities will be scored by 4 individual reviewers and inter-observer agreement will be determined. The reference standard will be histology or clinical follow-up. A questionnaire regarding patients’ experience with both modalities will also be completed at the end of the follow-up year.

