### Image analysis

Only PET-CT and 4-phase liver CT images will be analysed and used in the context of routine patient care during clinical follow-up. The PET-MRI images will not be part of the diagnostic and follow-up process.

For imaging analysis, blinded data sets of all scans will be viewed both separately and independently by two designated, experienced radiologists and two nuclear medicine physicians. The reviewers will be blinded to the results of the other imaging modalities and to final patient outcome. A time-interval of at least four weeks will be introduced between the first and second review. Progressive disease will be scored on a per-patient and per-lesion basis, and results of all imaging modalities will be compared. The criteria for progression on different modalities are defined in Table 
3. Each lesion on each modality will be scored on a separate form and results will be scored from 1–5 (Table 
4) and size and location of the lesions will be reported. A LTP is defined as a lesion located in or within 1 cm of the ablation zone; a new intrahepatic lesion is defined as a lesion located more than 1 cm distant from the ablation zone
[6]. On MRI, a suspicious lesions has to meet the definition of LTP in at least two different sequences before it is considered positive for progression.

**Table 3 T3:** Test positivity criteria for progressive disease on different imaging modalities; ≤1 cm of the ablation zone (LTP) / >1 cm of the ablation zone (new intrahepatic recurrence)

ceCT		Newly detectable hypodense lesion
MRI	T1	New focal hypo-intense lesion
	T2	New focal hyper-intense lesion
	Contrast enhanced	Irregular peripheral enhancement pattern of a circumscribed lesion
	Diffusion weighed	Lesion with high signal intensity on b800
FDG PET		Lesion with clearly increased focal uptake as compared to liver background

**Table 4 T4:** Study form for reviewers’ results (per lesion base)

**Study number:**		**Reviewer number:**
**Score**	**Definition**	**Explanation**
1	Normal	Confident that no tumor recurrence is present in the ablation zone/confident that no new intrahepatic lesions are present
2	Probably benign	The appearance of the ablated lesion is compatible with post-ablational inflammation or rim-like characteristics/the new lesions diagnosed do not appear malignant

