### Statistical analysis

We will determine the accuracy of PET-MRI for diagnosing recurrent disease compared to each imaging method (MRI, CT and PET-CT) and compared to pathology or clinical follow-up. Continuous variables will be summarized with standard descriptive statistics including means, standard deviations, medians and ranges when indicated. Categorical variables will be summarized with frequencies. McNemar’s test is used to determine agreement between PET-MRI and other modalities. The inter-observer variability will be quantified with Cohen’s Kappa and proportions of specific agreement. P-values less than 0.05 will be considered statistically significant. Statistical analysis will be performed using SPSS version 20.0 (SPSS Inc, Chicago).

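### McNemar's test, the only modality comparison named, takes one yes/no pair per patient or lesion, so the four reads collected on every scan are used less precisely than a reader-averaged comparison would allow.

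*Protocol article*

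**What the plan says.** The Image analysis section states that "blinded data sets of all scans will be viewed both separately and independently by two designated, experienced radiologists and two nuclear medicine physicians". The abstract confirms that this covers each imaging method: "The results of all modalities will be scored by 4 individual reviewers". So there are four reads per scan on every modality, by two radiologists and two nuclear medicine physicians.

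The Statistical analysis section names one between-modality test: "McNemar’s test is used to determine agreement between PET-MRI and other modalities". The only analysis it names for the multiple reads is agreement: "The inter-observer variability will be quantified with Cohen’s Kappa and proportions of specific agreement". The unit is both patient and lesion ("Progressive disease will be scored on a per-patient and per-lesion basis"), and the significance threshold is 0.05, with sidedness not stated. The article does not say how four reads become the single positive or negative result that McNemar's test needs.

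**The concern.** McNemar's test takes one binary pair per independent unit. Four reads of the same scan are made independently but are statistically correlated, because they are reads of the same case. They cannot enter the test as four separate pairs. That leaves three routes: choose one reader, run the test once per reader, or collapse the four reads to one call. None of them uses the reads as fully as averaging the paired difference over readers.

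This matters because cases are few. The sample size section uses a rate of 0.35 in 20 patients, so about 0.35 × 20 = 7 patients with LTP are expected, and it treats 5 as enough for a meaningful comparison. Reader noise adds directly to the variance of the sensitivity and specificity differences. Averaging over reads already planned removes part of it without another patient or scan. The point is lost precision, not inflated type I error.

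**Working it through.** **Inputs from the protocol article.** Four readers on all modalities (Abstract; Image analysis). n = 20 and LTP rate 0.35 (Sample size calculation). Sensitivities of 93% and 76% come from a Background study of hepatic metastases using post hoc image fusion; they serve only as illustration and are not a design assumption.

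**Inputs not in the article (assumed).** The correlation ρ between two readers' PET-MRI minus PET-CT differences on the same case, taken over 0.1 to 0.8; two-sided testing at 0.05.

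**Step 1: the plan's own figure.** P(X ≥ 5) for Binomial(20, 0.35) = 0.8818, which reproduces the stated 88%.

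**Step 2: one reader against the mean of four.** For each case and reader let d = (PET-MRI correct) − (PET-CT correct), with variance σ² and common between-reader correlation ρ. The mean of four reads has variance σ²(1 + 3ρ)/4. The ratio of the single-read variance to it is 4/(1 + 3ρ).

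| ρ | 4/(1 + 3ρ) |
|---|---|
| 0.1 | 4/1.3 = 3.08 |
| 0.3 | 4/1.9 = 2.11 |
| 0.5 | 4/2.5 = 1.60 |
| 0.8 | 4/3.4 = 1.18 |
| 1.0 | 4/4 = 1.00 |

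The ratio exceeds 1 for any ρ below 1. Running McNemar reader by reader gives four results, each with the single-read variance, and no combined estimate.

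**Step 3: pooled calls.** A latent probit reader model (200,000 cases, 93% versus 76%, ten settings) gave between-reader kappas of 0.32 to 0.74, ρ of 0.12 to 0.69 and single-reader ratios of 2.92 to 1.30. In the same settings:

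| Call | Mean difference (true reader average 0.17) | Variance relative to four-reader mean |
|---|---|---|
| ≥ 2 of 4 positive | 0.11 to 0.16 | 1.15 to 1.63 |
| ≥ 3 of 4 positive | 0.18 to 0.21 | 1.37 to 2.75 |

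The pooled calls estimate different differences, so variance alone is not a fair comparison. On squared difference over variance, relative to one reader, the ≥ 2-of-4 call scored 0.80 to 0.94, the ≥ 3-of-4 call 1.12 to 1.64, and the four-reader mean 1.30 to 2.92. The four-reader mean was ahead of both pooled calls in every setting.

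**Step 4: scale at this sample size.** Take the setting with single-read variance 0.215 and four-read variance 0.106. With 7 LTP the standard deviation of the sensitivity difference is √(0.215/7) = 0.175 for one reader and √(0.106/7) = 0.123 for the mean. Simulation with the number of LTP drawn from Binomial(20, 0.35), case share of latent variance 0.3–0.6 and case-by-modality share 0.2–0.4 (both assumed; 3,000 runs per setting) gave 0.17–0.19 against 0.11–0.15.

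**Step 5: power in the same kind of simulation.** Exact McNemar on one reader was compared with a sign-flip test over patients on the four-reader mean.
- 76% versus 93%: about 0.2% for one reader and 2–5% for the four-reader mean (1–6% in a repeat run); McNemar on a ≥ 3-of-4 call gave 0.3–0.4%.
- 60% versus 93% (assumed): 2–3% and 10–26%; the ≥ 3-of-4 call gave 3–6%.
- Equal sensitivities: the sign-flip test rejected in at most 1% of runs.

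**Step 6: the floor.** With 5 LTP patients, the smallest two-sided p is 2 × 0.5⁵ = 0.0625 for exact McNemar and 2/2⁵ = 0.0625 for the sign-flip test. With 6 both reach 0.031. P(X ≤ 5) = (1 − 0.8818) + 0.1272 = 0.245, so in about a quarter of trials of this size neither per-patient sensitivity test can reach 0.05.

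**The case against.** The strongest reply is that the article never says one reader enters the test. Rules for combining reads are commonly left to a fuller document, and a consensus or majority call would use all four reads in part. A reader might infer that the trial analyses one reader and so carries a known penalty of, say, 1.4 to 2.6 times the variance needed. The documents do not support that. They name no single-reader analysis and give no reader correlation, and 1.4 to 2.6 is only what ρ between about 0.62 and 0.18 would produce. Nor can it be said that most reader information is lost whichever route is taken: for a ≥ 2-of-4 call the variance is only 1.15 to 1.63 times that of the mean.

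Further objections stand in part. McNemar's test yields a p-value, and nothing in the article forbids also reporting reader-averaged sensitivity and specificity. The simulations use one LTP per patient and one scan, whereas the plan also scores lesions and scans three-monthly. The study calls itself observational and is sized on event counts, not power. Giving four readers from two specialties equal weight is a choice, and specialty-specific reads are also defensible.

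These points limit the size of the claim, not its direction. The finding does not rest on the missing combination rule, because each of the three routes through the named test is less efficient than the reader average.

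**Conclusion.** The point holds in a limited form. The named test does not make full use of the four-reader design, and a reader-averaged paired comparison is more precise at no cost in patients, scans or reads. The single-reader penalty is about 3.1 to 1.2 times the variance over the assumed ρ of 0.1 to 0.8, and it vanishes as readers approach perfect agreement. The pooled-call figures rest on the assumed latent model and the illustrative 93% and 76%.

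It would be wrong to conclude that averaging rescues the significance test. With the only sensitivities the article supplies, power remains in single figures, and the 0.0625 floor at 5 LTP applies to both tests. The benefit is a narrower estimate of the difference.

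**What to change.** In the Statistical analysis section, define the main PET-MRI versus PET-CT comparison as follows. For each patient, take the mean over the four readers of (PET-MRI correct minus PET-CT correct), separately for reference-positive and reference-negative patients. Report the resulting differences in sensitivity and specificity with patient-level intervals, and cluster per-lesion results by patient. Test with an exact sign-flip permutation over patients. Show radiologists and nuclear medicine physicians separately as a descriptive split, and keep reader-specific McNemar results as supportive.

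The cost is a paragraph of text and a short script outside the standard SPSS menus. Inference is then to the average of these four readers, which the text should say.

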[12]. PET-MRI appears to offer higher lesion conspicuity and diagnostic confidence compared to PET-CT
[13], and this additional information can influence clinical management of cancer patients The combined advantages of detection of smaller hepatic tumours with a higher sensitivity and detection of focal FDG uptake suggestive for LTP indicates that PET-MRI could provide complementary information and facilitate improved clinical decision making
[14].

To the best of our knowledge, the effectiveness of integrated PET-MRI in RFA or MWA follow-up has not been investigated. The primary aim of this study is therefore to determine the accuracy of 18 F-FDG PET-MRI in LTP detection. Secondary aims will be to investigate whether PET-MRI is more accurate than PET-CT and ceCT in the detection of new intra-hepatic lesions, and to evaluate inter-observer variability, the impact of PET-MRI on future treatment and patients’ views on both modalities. We hypothesize that PET-MRI will be at least equivalent to PET-CT in the diagnosis of LTP, but superior to PET-CT in the early detection of new intrahepatic lesions and therefore able to positively influence decision making in patients with RFA/MWA-treated CRLM.

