### Primary and secondary objectives

We will assess the effectiveness of FDG PET-MRI in the follow-up of thermal ablation (RFA/MWA) of CRLM. Our primary aim will be to assess the accuracy of FDG PET-MRI in the diagnosis of local progression in the first year after RFA/MWA of CRLM. Therefore, all FDG PET-MRI images will be compared to FDG PET-CT and 4-phase liver CT images, which are the current standard of care. Results of different imaging sets will be compared on a per-patient and a per-lesion base. These results will then be compared to a reference standard: either histological outcome (if available) or clinical follow-up.

Secondary outcomes will include the accuracy of diagnosis of new intrahepatic disease after RFA/MWA. Since only a single 18 F-FDG per combined PET-MRI and PET-CT visit will be applied, we will have the opportunity to investigate whether dual-time point PET can increase the specificity of the 18 F-FDG signal and increase diagnostic accuracy
[15]. The reproducibly and robustness of inter-observer variation will also be determined. Clinical relevance will be studied by recruiting a panel consisting of a radiologist, interventional radiologist, nuclear medicine physician, oncologist, oncological surgeon and a radiation oncologist to retrospectively review PET-MRI images and agree on the preferred treatment. Choice of treatment based on PET-MRI will then be compared to the treatment that was actually received based on PET-CT and 4-phase liver CT. Finally, patients’ preferences will be assessed at one year follow-up using a specifically designed questionnaire that compares both modalities (Table 
1).

**Table 1 T1:** Questionnaire comparing PET-CT and PET-MRI (completed following fourth PET-MRI)

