### Sample size calculation

Sample size estimates are based on the incidence of local site recurrences and new intrahepatic metastases. Previous studies have shown that 25-40% of the patients treated with RFA/MWA develop LTP, of which >95% occur within the first year
[4]. In addition, 30-40% of the patients will develop new intrahepatic metastases
[2,21]. At least 5 LTP and 5 new intrahepatic lesions are necessary for a meaningful comparison between PET-CT and PET-MRI in this observational study. Using the binominal distribution (with *p* = 0.35 and n = 20), the chance of finding 5 LTP and the chance of finding 5 new intrahepatic lesions in our population are both 88%. This suggests that the study has a satisfactory chance of success with a sample size of 20 patients. Patients excluded during the study period will be replaced by new participants, so that 20 patients will have completed one year follow-up at study completion.

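### McNemar's test is assigned to show agreement between modalities, which it does not measure; as the only between-modality test named, it also cannot support the hypothesis that PET-MRI is at least equivalent to PET-CT for LTP

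*Protocol article*

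**What the plan says.** The Statistical analysis section names one test for comparing modalities and gives its purpose: McNemar's "test is used to determine agreement between PET-MRI and other modalities". The decision rule is "P-values less than 0.05 will be considered statistically significant"; sidedness is not stated. True agreement statistics do appear, but for readers only: "The inter-observer variability will be quantified with Cohen" opens the sentence that assigns kappa and proportions of specific agreement.

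The section on objectives states the primary aim: "Our primary aim will be to assess the accuracy of FDG PET-MRI in the diagnosis of local progression in the first year". The Background closes with a two-part hypothesis: that "PET-MRI will be at least equivalent to PET-CT in the diagnosis of LTP", and that it will be "superior to PET-CT in the early detection of new intrahepatic lesions". The article gives no equivalence or non-inferiority margin and no confidence-interval criterion.

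The Sample size calculation rests on a count of events: "At least 5 LTP and 5 new intrahepatic lesions are necessary for a meaningful comparison between PET-CT and PET-MRI".

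**The concern.** Two things do not fit together.

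First, the test and its stated purpose. McNemar's test uses only the two discordant counts and asks whether they are balanced. Two modalities that contradict each other often, but equally in both directions, give a p-value near 1. Two that almost always agree can give a small one. The p-value therefore says nothing reliable about agreement.

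Second, the test and the LTP hypothesis. A test of no difference without a margin can at best show a difference. Failing to find one does not show that PET-MRI is at least as good, least of all with very few LTP.

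At stake is the interpretation of the main comparison. A non-significant McNemar result is close to certain here whatever the truth, and the stated purpose of the test invites readers to take it as reassurance.

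**Working it through.** **Inputs.** From the Sample size calculation: n = 20, event probability 0.35, at least 5 LTP. From the Statistical analysis section: significance at 0.05. Assumptions made here: two-sided testing, one LTP per patient, independent pairs.

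**1. The plan's own figure.** P(X ≥ 5) for a binomial with n = 20 and p = 0.35 is 0.8818, which reproduces the stated 88%. (P(X = 5) is 0.127, so at least 5 is meant.) The expected number is 20 × 0.35 = 7 LTP.

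**2. What McNemar's test responds to.** Let b and c be the counts positive on one modality only. Exact two-sided p = min{1, 2 × P(Bin(b + c, 0.5) ≤ min(b, c))}. The concordant cells do not enter. Kappa = (observed − expected agreement) / (1 − expected agreement).

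| Both + | PET-MRI only | Other only | Both − | Disagreement | Kappa | McNemar p |
|---|---|---|---|---|---|---|
| 5 | 5 | 5 | 5 | 50% | 0 | 1.00 |
| 0 | 10 | 10 | 0 | 100% | −1 | 1.00 |
| 60 | 8 | 0 | 132 | 4% | 0.91 | 0.008 |

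For the last row, observed agreement is 192/200 = 0.96, expected agreement is (68 × 60 + 132 × 140)/200² = 0.564, and kappa = 0.396/0.436 = 0.91. The p-value and the agreement move independently. The tables are constructed to show this and are not forecasts.

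**3. Smallest attainable p for sensitivity.** Only reference-positive cases count.
- 5 LTP, all discordant one way: 2 × 0.5⁵ = 0.0625, not significant.
- 6 discordant, all one way: 2 × 0.5⁶ = 0.031.
- 6 against 1: 2 × (1 + 7)/2⁷ = 0.125, not significant.

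So significance is impossible with 5 LTP. With the expected 7, it needs at least 6 discordant one way and none the other.

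**4. If PET-MRI were truly worse.** Suppose a fraction d of LTP are found by PET-CT and missed by PET-MRI, with no discordance the other way. With 7 LTP, power = 7d⁶(1 − d) + d⁷.
- d = 0.20: 0.00036 + 0.00001 = 0.0004.
- d = 0.40: 0.0172 + 0.0016 = 0.019.

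Even a 40-point deficit would give p > 0.05 in about 98% of such studies.

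**5. What the data could say by estimation.** If PET-MRI misses none of the LTP found by PET-CT, the one-sided 97.5% upper bound on the proportion so missed is 1 − 0.025^(1/n): 52% for n = 5 and 41% for n = 7.

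**6. Scale of a margin-based claim.** The article gives no margin, so this is an assumed range. For paired non-inferiority with one-sided 0.025, 80% power and no true difference, n = ψ(1.96 + 0.84)²/margin², where ψ is the discordant fraction. With ψ from 10% to 30%, this needs about 20 to 59 LTP at a 20-point margin and 79 to 236 at a 10-point margin, against 5 to 7 here.

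**The case against.** Four counter-arguments deserve weight.

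- **The misreading is not written down.** A reader might infer that p > 0.05 will be reported as agreement or equivalence. No section says so; the article only defines significance, and it also plans frequencies for categorical variables. This stands. The point is that the plan leaves the misreading open, not that it commits to it.
- **The reference standard is not ignored.** A reader might infer from the McNemar sentence alone that modalities are compared without regard to truth. The objectives, the Statistical analysis section and the Discussion all plan accuracy against histology or clinical follow-up. This stands. What is open is whether McNemar's test runs on raw positivity or within reference-positive and reference-negative cases. A journal article may leave that to a fuller document.
- **Equivalence is not the declared primary objective.** The primary aim is accuracy. The equivalence hypothesis closes the Background, and its second half is a superiority hypothesis, for which McNemar's test is suitable. An unseen SAP might hold a margin. This stands too, and limits the remedy to wording.
- **The Background sensitivities of 93% and 76% prove little here.** They make power at 7 LTP tiny (0.00065 if the modalities err independently). But they assume that PET-MRI is better, in which case the equivalence hypothesis would be true and non-significance would mislead no one. They also come from post hoc fused imaging of hepatic metastases. The argument above therefore does not use them.

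None of this rescues the stated purpose. Calling McNemar's test a measure of agreement is wrong as written, whatever a SAP adds.

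**Conclusion.** The point holds in a limited form. The purpose given to McNemar's test is wrong: 50% disagreement in 20 patients can yield p = 1.00. As the only between-modality test named, it also cannot support the equivalence hypothesis for LTP. With 5 LTP, no comparison of sensitivity can be significant (minimum p = 0.0625), so a non-significant result carries no information.

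The documents do not support saying that the plan will declare agreement or equivalence from p > 0.05, that it disregards the reference standard, or that McNemar's test has no place. It is mislabelled, not useless.

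The exact p-values rest on two-sided testing and one independent LTP per patient. Several lesions or repeated 3-monthly scans per patient would add pairs but break independence. The power figures in step 4 and the sizes in step 6 depend on the stated assumptions; the p-value floor with 5 LTP does not depend on any assumed sensitivity.

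**What to change.** Replace the McNemar sentence in the Statistical analysis section with text to this effect:

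- **Difference.** Sensitivity is compared among reference-positive cases and specificity among reference-negative cases. Paired differences are reported with 95% confidence intervals, with exact McNemar as the supporting test of difference.
- **Agreement.** Agreement between PET-MRI and each other modality is reported with kappa and proportions of specific agreement, the statistics already planned for readers.
- **Interpretation.** A p-value above 0.05 will not be taken as agreement or equivalence. The hypothesis that PET-MRI is at least equivalent for LTP is treated as estimation only, unless a margin is fixed in advance and judged against the confidence limit.

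The cost is analysis wording; patients, scans and data are unchanged. The downside is that with about 5 to 7 LTP the intervals will be wide and the conclusion more modest.
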